#### Recruitment

Recruitment began in June 2018 and will end in June 2021. On completion of the training session, patients are asked if they are interested in participating in the study. The trainer provides the patient with written and oral information about the study and how patient confidentiality will be protected. The trainer should also be able to answer questions raised by participants. If not, the project leaders are to be contacted without delay. Interested patients will then provide a written informed consent where upon they will be asked to fill in baseline questionnaire. Individuals declining study participation will access the same OPEND model as the individuals entering the study, and no compensation is given to the study subjects. The informed consent provided by included patients in the cohort study includes the follow-up in register data (national patient register and regional hospital and ambulance registers) for a three-year period, and register follow-up is carried out during the full three-year period, unless the patients contacts the researchers in order to withdraw consent. In case a patient ceases to show up in OST or NEP facilities in the region, only the self-report data regarding witnessed overdoses and naloxone administration will be dropped from further data collection.

#### Quantitative data collection

Included subjects in the cohort-specific analyses will be followed for 36 months. Questionnaires are obtained from initial training, on follow up, every sixth month, and upon THN refill, for any reason.

#### Measures

In order to distinguish acute drug-related deaths from deaths caused by diseases and organ damage caused by long-term use, and data from emergency and prehospital healthcare, collecting data on mortality, cause of death, and toxicological raw data, information will be gathered from the following registers:
The National Board of Health’s Death Causes Register stores diagnostic information on mortality and causes of death such as international disease classification codes, ICD codes.The National drug index (linked to the National Board of Health’s death cause register), containing information on deceased persons, where drug addiction or drug poisoning is mentioned on the cause of death certificate, either as underlying or contributing cause.The National registry data for F1 diagnosis (ICD-10 - diagnoses related to harmful use or substance dependence) [89], for enabling interconnection of national mortality data with the presence of such diagnosis, in order to correctly identify deaths in individuals with substance use historyThe Public Health Agency’s research register Toxreg is based entirely on toxicological raw data, which is taken by routine when investigated by forensic medicine. Ninety three per cent of all unnatural / violent deaths among persons under the age of 65 are examined medically in Sweden, which means that the majority of all acute drug-related deaths can be found in Toxreg (the Public Health Authority, 2015).Skåne’s County medical and administrative registers for diagnoses and intervention codes indicating a condition of drug poisoningData for all fatal and non-fatal overdose cases attended by ambulance in the region will be identified (including vital status of cases upon ambulance attendance) from a regional electronic documentation system for prehospital units in the Skåne County, where clinical data from ambulance-attended cases, and treatments given by ambulance staff, are documented. This data source covers the full intervention period in the study, but the electronic documentation system was introduced in early 2017, such that the comparison period can include this type of data only since then.Data from emergency hospital departments at hospitals in the region, describing all cases of overdose events who attend hospital (identified through diagnostic codes).

Regarding self-report data in the cohort study, surveys are administered to the research subjects during their visit to units, included in the project, distributing naloxone at six, 12, 18, 24, 30 and 36 months, respectively, and / or at re-supply (any cause). The enrolment data include information concerning demographics, own substance use during the last 30 days, previous experience of either witnessing an overdose and/or own experience of overdose and questions on recognition of, and handling of an overdose (*Questionnaire 1 see* Additional file 1).

Data collected upon naloxone refill concerns what happened to the previous naloxone/kit, for instance if it was stolen, lost, or used on oneself or on someone else. If it was used to reverse an overdose, questions on whom was it used and where did the overdose took place (private/or public space), will follow. Questions concern how to recognize an overdose, what to do if an overdose occurs to someone else, own substance use during the last 30 days, where naloxone is kept and if he/she sometimes are unaware of the content of their drugs, followed by statements concerning drug use, safety of naloxone, assessment of own risk behaviour and response to a potential or witnessed overdose (*Questionnaire 2–4 see* Additional files 2, 3 and 4).

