#### Secondary outcome measures

##### Secondary outcome measures in the general population

Reaction level of ambulance-attended opioid overdose survivors in the general population. Assessment of responsiveness in acute brain disorders using Reaction Level Scale (RLS-85) in ambulance. The RLS scale is graded from 1 (awake, no delayed reaction, oriented) to grade 8 (unconscious, no movements to painful stimuli) [Time Frame: 2019–2023].Respiratory rate of ambulance-attended opioid overdose survivors in the general population. Respiratory rate (breaths per minute) registered in ambulance [Time Frame: 2019–2023].Heart rate of ambulance-attended opioid overdose survivors in the general population. Heart rate (beats per minute) of opioid overdose survivors registered in ambulance [Time Frame: 2019–2023].Naloxone or other antidote administered by ambulance staff to ambulance-attended opioid overdose survivors in the general population [Time Frame: 2019–2023].Need of ambulance transport to hospital of ambulance-attended opioid overdose survivors in the general population, information registered in ambulance [Time Frame: 2019–2023].Incidence of opioid overdoses attended by ambulance or emergency hospital care (i.e. including non-fatal overdose cases), information registered in ambulance or from diagnostic codes registered in emergency hospital departments [Time Frame: 2019–2023].

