### Statistical methods

Comparison of mortality, before and after intervention, is done by Poisson regression with an indicator variable for the intervention (0 = comparison, 1 = intervention), adjusting for age and gender distribution. The effect is described as RR (relative risk), with 95% confidence intervals. *P* values < 0.05 will be considered as statistically significant. The primary outcome measure relates to mortality in the overall cohort. The effect on mortality will be studied in OST and NEP separately, using a subgroup analysis. The evidence in effect between the cohorts will be described by the *p*-value of an interaction test. Outcomes are studied year by year during the intervention period, compared to the comparison period, year by year.

For the study aims regarding the included cohort, this is open, dynamic cohort based on individuals in OST and NEP, where they contribute with person time, as at-risk from entry to study end or death, or by possible exit from the cohort (the earliest of these three events is the end date of the personal time calculation). In the general population analyses, 2013 to 2017 constitute the comparison period, while corresponding data, during 2019–2023, constitutes the intervention period.

Each person included in the follow-up will contribute a record (row) in the research database for each year this person is included in one of the two cohorts. In the row, in addition to each individual’s consecutive number, variables such as date, sex, age, cohort (1 = OST, 2 = NEP), intervention (0 = comparison, 1 = intervention), person time, date in the event of death, and status (alive/dead) at the end of each year, will be registered. In addition, based on public registers of the number of patients in OST, in the analyses it will be possible to control for fluctuations in OST availability (number of patients in methadone and buprenorphine treatment, respectively) in the region, as OST availability is likely to affect mortality rates; for example, based on national register data from the present setting, it has been shown that the risk of overdose mortality varies depending on OST status [90].

Significance, as above, is 5%, when applying a double-sided test. The target for the statistical strength is set at 80% for primary outcome. Secondary outcome and subgroup analyses have not been calculated in strength.

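### The combined ambulance-or-hospital overdose incidence has a mixed-source baseline: ambulance data enter 2013–2017 only from early 2017, so a pooled before/after ratio would be biased upward

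*Protocol article*

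**What the plan says.** All references are to the protocol article.

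- **Statistical methods** fixes the windows: "In the general population analyses, 2013 to 2017 constitute the comparison period, while corresponding data, during 2019–2023, constitutes the intervention period". That section makes no exception by outcome or data source.
- **Secondary outcome measures in the general population** defines an either-source count: "Incidence of opioid overdoses attended by ambulance or emergency hospital care". Its cases come from ambulance records or from emergency department diagnostic codes. The only time frame attached to it is 2019–2023.
- **Measures** says of the ambulance system that "This data source covers the full intervention period in the study", but also that "the electronic documentation system was introduced in early 2017, such that the comparison period can include this type of data only since then".
- **Study aims** names the effect on the incidence of non-fatal overdoses in the general population as a secondary aim, within a study that compares an intervention period with a historical one.
- **Statistical methods** also plans to look at outcomes year by year in both periods.

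**The concern.** A count built from two sources is comparable over time only if both sources run throughout. Here the second source is absent for roughly the first four of five baseline years and present in every intervention year. A second source can only add events, so the baseline rate is understated relative to the intervention rate whenever some overdoses appear in the ambulance record alone.

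The protocol itself foresees such cases. One of its other outcomes is "Need of ambulance transport to hospital of ambulance-attended opioid overdose survivors in the general population", which presupposes that some attended survivors may not be taken to hospital. The ambulance data also include fatal cases, and a death at the scene might never receive an emergency department code.

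At stake is the reading of a named secondary effect measure. The pooled ratio could hide a true reduction in attended overdoses, or suggest an increase, because ascertainment widened.

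**Working it through.** **The plan's own figures.** The protocol states no figure for this outcome. Its only design calculation is power for mortality. A two-sided 5% comparison of two proportions with 8000 and 3000 person years gives 80.6%, 80.5% and 57.0%, against the stated 81%, 81% and 57%. Those figures reproduce and do not bear on this point.

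**Inputs**
- Baseline length: 5 years, 2013–2017 (Statistical methods).
- *y*, years of ambulance data inside the baseline: early 2017 to the end of 2017 (Measures). The month is not given, so I take 12 months as the upper limit and 9 months as an assumed lower value.
- *s*, the share of combined-outcome events recorded by ambulance only: not in the protocol. Assumed 10–40%.
- Ambulance coverage of the intervention period: complete (Measures).

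**Formula.** With a constant true rate, the fraction of baseline events captured is

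capture = [(5 − y)(1 − s) + y] / 5

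and the rate ratio with no true change is 1 / capture. This is a ratio of rates with full capture after baseline, so the length of the intervention window does not enter.

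**Results**

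| s (assumed) | capture, y = 1 | null ratio, y = 1 | capture, y = 0.75 | null ratio, y = 0.75 |
|---|---|---|---|---|
| 10% | (4 × 0.9 + 1)/5 = 0.92 | 1.09 | 0.915 | 1.09 |
| 20% | (4 × 0.8 + 1)/5 = 0.84 | 1.19 | 0.830 | 1.20 |
| 30% | (4 × 0.7 + 1)/5 = 0.76 | 1.32 | 0.745 | 1.34 |
| 40% | (4 × 0.6 + 1)/5 = 0.68 | 1.47 | 0.660 | 1.52 |

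At s = 0 the ratio is 1.00 and there is no bias.

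**Masking of a true effect.** Borrow the protocol's mortality effect of RR 0.75 purely for illustration. With y = 1 the observed ratio is 0.75/0.92 = 0.82 at s = 10%, 0.75/0.84 = 0.89 at 20% and 0.75/0.76 = 0.99 at 30%. The reduction disappears when capture equals 0.75, that is at s = 0.25 × 5/(5 − y): 31% for y = 1 and 29% for y = 0.75.

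**Matched sources.** If both periods use the same sources, the null ratio is 1.00 for every s. The price is a shorter baseline. With a constant yearly event rate, the standard error of the log rate ratio is proportional to √(1/years before + 1/years after). Against a five-year baseline and five intervention years:
- 12 baseline months: √(1 + 0.2)/√(0.2 + 0.2) = √3 = 1.73
- 10 baseline months: √(1.2 + 0.2)/√(0.2 + 0.2) = √3.5 = 1.87

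The Trial status section starts the intervention period on 1 July 2019. With 4.5 intervention years the factors are 1.70 and 1.84.

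**The case against.** The strongest reply is that the Measures section already discloses the gap. On that reading, Statistical methods gives the general window and Measures shortens it for ambulance data. This stands for the five outcomes drawn only from ambulance records (reaction level, respiratory rate, heart rate, antidote, transport). It does not settle the combined outcome. Letting ambulance data into the comparison period only from early 2017 is exactly what produces the mixed series, and nothing separates the sources or shortens the window for that outcome.

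A second reply is that no sentence states a pooled contrast for incidence. The Poisson model is described for mortality, and the incidence outcome carries only a 2019–2023 time frame. This is fair, and it makes the bias conditional on pooling. But the protocol does fix the composite, the two windows and the aim of estimating an effect on incidence. The problem is how these fit together, not a detail left for an analysis plan.

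A third reply is the year-by-year display. It could show a step inside the baseline, and comparing 2017 with the intervention years would be close to like with like. It would not correct the pooled ratio.

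Some stronger inferences are tempting but not supported:
- *Incidence would jump at launch.* The ascertainment step falls in early 2017, more than a year before the June 2018 launch. It resembles a post-launch rise only in the pooled contrast.
- *All general-population outcomes are biased.* Mortality comes from national registries, and the five ambulance-only outcomes use one source in both periods.
- *The 2017 ambulance data are incomplete.* Nothing in the protocol documents under-recording in the system's first year.
- *The unused months of 2018 before launch clearly belong in the baseline.* This is debatable. Naloxone could be ordered from April 2018, key trainers were trained in March and April 2018, and a partial calendar year would be added.

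**Conclusion.** The point holds for one secondary outcome, the combined incidence of overdoses attended by ambulance or emergency hospital care. Under the stated windows, a pooled 2013–2017 versus 2019–2023 ratio compares about four hospital-only years and at most one two-source year with an intervention period that has both sources throughout.

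The upward direction follows from the definitions, provided at least some overdoses are ambulance-only. The size does not: 1.09–1.47 rests wholly on the assumed 10–40% share with 12 months of ambulance baseline. It would be near zero if almost every attended case also received an emergency department code.

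The five ambulance-only outcomes have a baseline of at most one year. That is a disclosed limit on precision, not this bias. The primary outcome is unaffected. The change is worth making, but it does not threaten the main conclusion of the study.

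**What to change.** State a baseline window for each general-population outcome and source:

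1. Report hospital-coded overdose incidence for 2013–2017 against the intervention period, with emergency department codes as the only source in both.
2. Restrict ambulance-attended incidence and the combined measure to the time when both sources exist. For the baseline this means from the start of the electronic system in early 2017 to the end of 2017. Give the start month.
3. Present the two series side by side, and say that no pooled ratio will mix hospital-only and two-source years.

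The cost is mainly wording. The statistical price is a short baseline for the combined measure, with a standard error of the log rate ratio about 1.7 times that of a five-year baseline and somewhat more if the system started some months into 2017. The hospital-only series has its own weakness: it could fall simply because bystander reversal reduces transport to hospital. Neither series should therefore be read alone.

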### Data analysis

#### Data storage and missing data

Collected data from active intervention participants are registered in an electronic Case Report Form (e-CRF). A unique e-CRF is created for each active participant, separated from the identification of the study participant, and stored in the clinical trial software RedCap. Data are stored confidentially and cannot be accessed by anybody outside the study staff. All questions in the e-CRF are to be answered actively, if questions are not replied to, they shall be marked as NA = “Not applicable” or NK = “Not known”.

During the first 5 months data was collected on paper, as the use of the computerized application was delayed. In November 2018, each unit received their own iPad, which was provided for by the project, containing the RedCap application. Patient information and consent is still provided on paper. The 5 months of data collected on paper will be entered in the e-CRF by a research administrator at Lund University.

There will be no registration of individuals declining naloxone training. During the 3 years that the project will be running, individuals could have visited many of the sites, and have, most likely been asked on several occasions. However, aggregated data from OST and NEP facilities in the region will enable descriptions of whether included participants differ from these overall populations on a group level.

Statistical data are drawn from available data registers. Each individual included by follow up will contribute to the research database with one entry (row) for each year, in either cohort. During the follow up period, person-time time after cohort regression, will not be taken into account.

### Trial status

In July 2018, 3 weeks into the project, 70% of targeted units (*N* = 24) were included, providing OPEND and including subjects into the study. Five weeks into the project 87% of targeted units had started, after 12 weeks, all units were including patients in the project. After inclusion and establishment of the first targeted 24 units, making sure the program is well established into daily management, the naloxone project has recently included another 3 units, and are planning on further expansion. So far, reports from included units are indicating that upon completion of training, approximately 80% of patients are giving their consent to study inclusion. The intervention period begins 1 July 2019 (with the first analyses conducted for general population data for the 18-month period of 1 July 2019–31 December 2020), based on the assumption that the naloxone distribution will be considered to have reached a satisfactory level from July 2019.

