### The Skåne naloxone project

In accordance with the decision of the Health Board in Skåne County in December 2014, the Director of Health was commissioned to monitor the possibilities of conducting a pilot study on THN with intranasal naloxone, and to report the case in March 2015. Skåne County has since followed the development of ongoing clinical studies and ongoing projects. In March 2015, The Director of Health was commissioned to start an experimental project as soon as possible in the form of a clinical study using intranasal naloxone spray. The pilot project was started after naloxone distribution was made legal by the authorities and after the nasal spray became available, and it is to be run for 3 years and during this time frame the scope of the study could be expanded if additional evidence was to be added [82].

Since prescription or distribution to a third party is prohibited by law, a well-structured and efficient multi-site implementation and distribution should provide the means to reach a large proportion of high-risk individuals with a relatively high likelihood of becoming bystanders at overdose situations. Implementation of this type of intervention setting where bystanders will administer naloxone and use life-supportive interventions as taught by the naloxone providers is believed to be feasible in a Swedish setting. The project was launched in the second quarter of 2018 [83]. The project is conducted by a steering group with representation from the organization of the county (Region Skåne) as well as the director of the clinical trials support organization of the region, as well as the principal investigator (the last author of the present paper), and the project leaders (the remaining authors of the paper). The current naloxone distribution program will continue for 3 years, and study outcomes will be followed for up to 5 years.

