#### Primary outcome measures

Mortality due to opioid intoxication in the general population in Skåne County in 2019–2023, compared with historical mortality due to opioid intoxication during 2013–2017. Number of deaths will be collected from national registries.

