#### Power and sample size

Power has been calculated only for the primary outcome measure. The total population at risk of fatal overdose in the general population is unknown, as people may be at risk of overdose death either because of a severe opioid dependence, a less severe state of dependence or a more unregular use of opioids. As the number of potentially affected individuals is unknown, the power calculations were based on numbers calculated from the number of individuals reached by the intervention at NEP and OST facilities. Thus, power calculations based on the cohort planned to receive distributed naloxone will be considered to be a minimum level with the possibility of a higher effect if the naloxone intervention disseminates also beyond the NEP and OST populations.

The number of patients in OST and NEP is estimated to comprise approximately 2000 individuals, 1000 individuals respectively. Power was calculated based on potential mortality in these two groups (calculated conservatively for 4 years prior to the intervention); a total of 4 × 2000 = 8000 person years; referred to as a ‘comparison period’), and with the conservative assumption that the intervention is calculated to reach the full study group for 1.5 years (intervention group, 2019–2020) (1.5 × 2000 = 3000 person years). The statistical power calculations are made with the Microsoft Excel sheet EPISHEET available for download at www.krothman.org/episheet.xls (downloaded on 14 January 2016).

Assuming that mortality before intervention is 50 deaths per 1000 person years in the overall cohort (that is, a 5% annual risk), a relative risk reduction of 25% (relative risk RR = 0.75) is required in order for the statistical strength to exceed 80% (81%), 5% significance limit, two-sided test, with 8000 person years before intervention (comparison period) and 3000 person years after intervention (intervention group). If however, assuming that mortality before intervention is 30 per 1000 person years in the overall cohort (that is, a 3% annual risk), a higher relative risk reduction, 32% (RR = 0.68), is required for the statistical strength to exceed 80% (81%), 5% significance limit, two-sided test, with 8000 person years before intervention (comparison period) and 3000 person years after intervention (intervention group). If the risk reduction still is 25%, even in this scenario, the statistical strength drops to 57%.

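### The primary intervention period starts in January 2019 in two sections and on 1 July 2019 in another, and no confirmatory test is named between the 18-month and five-year analyses

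*Protocol article*

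**What the plan says.** All references are to the protocol article.

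- **Primary outcome measures** define the outcome as "Mortality due to opioid intoxication in the general population in Skåne County in 2019–2023", compared with 2013–2017.
- **Statistical methods** repeat this for the general-population analyses: 2013 to 2017 is the comparison period, "while corresponding data, during 2019–2023, constitutes the intervention period". The model is a Poisson regression with one 0/1 intervention indicator, and p < 0.05 (two-sided) is the only significance rule. The section adds: "Outcomes are studied year by year during the intervention period".
- **Trial status** states: "The intervention period begins 1 July 2019". The reason given is an assumption that "the naloxone distribution will be considered to have reached a satisfactory level from July 2019". The same sentence plans an early look, "with the first analyses conducted for general population data for the 18-month period of 1 July 2019–31 December 2020".
- **Power and sample size** assumes, as a conservative basis, that "the intervention is calculated to reach the full study group for 1.5 years (intervention group, 2019–2020"), set against four comparison years.
- **The Skåne naloxone project** says: "The current naloxone distribution program will continue for 3 years, and study outcomes will be followed for up to 5 years". Launch was on 11 June 2018 (Structure of implementation).

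**The concern.** With a single 0/1 indicator, every death and every month of population time must be coded as comparison, intervention or excluded. Under Primary outcome measures and Statistical methods, January–June 2019 is coded 1. Under Trial status it precedes the intervention period. Both instructions cannot be followed. In a before–after comparison without a concurrent control, the dates are what define the contrast, so they should not be open to choice.

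Two things are at stake. First, months that the protocol itself regards as not yet adequately supplied may be counted as intervention, which would pull the RR towards 1. Second, the same outcome is to be analysed at 18 months and again over the full window under one 5% rule. Because the text does not say which result carries the claim, a positive 18-month result could be announced three years before the stated primary window closes.

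**Working it through.** **1. The plan's own power figures.** Inputs from Power and sample size: 8000 v 3000 person years, two-sided 5%. Two-proportion power with pooled null variance gives:

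| Rate per 1000 person years | RR | Stated | Recomputed |
|---|---|---|---|
| 50 | 0.75 | 81% | 80.6% |
| 30 | 0.68 | 81% | 80.5% |
| 30 | 0.75 | 57% | 57.0% |

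The figures reproduce. The 1.5 years used there equal the 18 months from 1 July 2019 to 31 December 2020 in Trial status, so these two sections agree with each other.

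**2. The windows side by side.** The conflict is between a January 2019 start (60 months to the end of 2023) and a July 2019 start (54 months to the same end). The months in dispute are 60 − 54 = 6.

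**3. Largest dilution from those six months.** If the effect is RR 0.75 from July 2019 to December 2023 and nil in January–June 2019:

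RR over five years = 1 − (1 − 0.75) × 54/60 = 1 − 0.25 × 0.90 = 0.775.

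This is an upper bound, since any effect in early 2019 brings it closer to 0.75.

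**4. What this does to power in the general population.** The protocol gives no regional death count, so two values are assumed:
- 114 per year, applying the national rate to the region: 92 per million × 1.3 million × 0.95 with opioids present = 113.6.
- 73 per year, an arbitrary lower value that the documents do not give.

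Wald power for log RR, with SE = √(1/D₀ + 1/D₁) and five comparison years:
- 60 months at RR 0.775, 114 per year: D₀ = 568, D₁ = 113.6 × 5 × 0.775 = 440, SE = 0.0635, z = 0.2549/0.0635 = 4.01, power 98%. At 73 per year: 90%.
- 54 months at RR 0.75, 114 per year: D₁ = 113.6 × 4.5 × 0.75 = 383, SE = 0.0661, z = 0.2877/0.0661 = 4.35, power 99%. At 73 per year: 94%.
- 60 months at RR 0.75 (effect already full in January 2019): 99% and 95%.

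The six months therefore move the estimate and the case count more than they move power.

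**5. Type I error of two unadjusted looks.** Both tests share the five comparison years, and the 18 months lie inside the five years. In units of one year's deaths under the null:
- variance, 18-month contrast: 1/5 + 1/1.5 = 0.867
- variance, five-year contrast: 1/5 + 1/5 = 0.400
- covariance: 1/5 + 1/5 = 0.400
- correlation: 0.400/√(0.867 × 0.400) = 0.68

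The bivariate normal probability that at least one |z| exceeds 1.96 is 8.4%. With a 54-month final window the correlation is 0.70 and the result is again 8.4%.

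**6. Months after the planned end of distribution.** Three years from June 2018 ends about June 2021. Of the 60 months in 2019–2023, 6 precede July 2019, 24 run from July 2019 to June 2021, and 30 follow. Power under three assumptions about the 36 months outside the middle block, at 114/73 deaths per year:

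| Effect outside the 24 months | RR, 2019–2023 | Power, 2019–2023 | Power, 24 months only |
|---|---|---|---|
| Persists to 2023 (nil only in January–June 2019) | 0.775 | 98%/90% | 91%/75% |
| Half | 0.825 | 87%/70% | 91%/75% |
| None | 0.90 | 41%/28% | 91%/75% |

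**The case against.** The best reply is that this is a small wording slip. Primary outcome measures and Statistical methods agree on 2019–2023. The 18 months appear only as a conservative power basis and as first analyses, neither of which redefines the outcome, and an analysis plan not shown may label the early and yearly results as descriptive. Much of this stands. There are not three rival windows, and the dilution is modest. What remains is that Trial status uses the term intervention period with a different start, and gives a substantive reason for it.

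A reader might infer three stronger points that the documents do not support.

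- **That most of the window is unexposed.** All 24 units were including patients 12 weeks after launch, so early 2019 was not without naloxone. No passage says that supply or effect ceases in June 2021. The protocol allows the scope to expand, reports added units, notes a national recommendation to offer take-home naloxone, and openly pairs three years of distribution with up to five years of outcomes. The 41%/28% power needs zero effect in 36 of 60 months.
- **That the primary window should be cut to 24 months.** That is a trade-off: better if the effect stops with distribution, worse if it persists.
- **That type I error is about 24%.** That figure counts five yearly comparisons as confirmatory tests. The text says only that outcomes are studied year by year, and does not make a single significant year a success.

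**Conclusion.** The start of the primary intervention period is contradictory, and this changes which deaths enter the primary rate ratio. The difference is six of 60 months. If they carry no effect, RR 0.75 becomes at most 0.775, with little loss of power at the assumed death counts.

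The protocol also plans an 18-month and a five-year analysis of the same outcome under one 5% rule without naming the confirmatory one. If both can support a claim, type I error is about 8.4%. This assumes equal underlying rates in both periods, Poisson variation, and no alpha split in a document not shown.

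The contradiction in dates rests on the text alone. The dilution and power figures rest on the stated assumptions about effect and regional deaths.

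**What to change.** 1. Use one start date in Primary outcome measures, Statistical methods and Trial status. By the protocol's own criterion this is 1 July 2019, with launch to 30 June 2019 treated as phase-in and excluded from both periods.
2. Name one confirmatory test: 1 July 2019–31 December 2023 against 2013–2017.
3. Report the 18-month and year-by-year results as descriptive estimates with confidence intervals. If the 18-month analysis is meant to support a claim, split alpha between it and the final test.
4. State in Power and sample size that 1.5 v 4 years is a conservative basis for power and not the primary window.
5. Add a sensitivity analysis limited to the months in which the programme distributes naloxone (1 July 2019 to about June 2021 as planned). It should not replace the primary window.

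The cost is wording, plus six fewer months of post-launch deaths in the primary test. At RR 0.75 throughout, 54 rather than 60 months changes power from 99.4% to 99.2% at 114 deaths per year, and from 95% to 94% at 73.
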